## Methods/design

### Aim

The primary aim of this study is to assess the feasibility of a proposed fully cluster randomised controlled trial of the effectiveness of ASBI in primary health care in Kazakhstan. The secondary aim is to explore the feasibility and acceptability of implementing ASBI in this setting from the perspective of patients and physicians.

Specific objectives are as follows:
To conduct a two-arm pilot feasibility cluster randomised controlled trial (cRCT) (with randomization at the level of PHCU) to assess the feasibility of a future definitive cRCT of ASBI in primary care in Kazakhstan;To explore the feasibility and acceptability of ASBI and trial processes to physicians and patients;To identify key determinants of ASBI implementation from the perspective of physicians and patients to identify specific facilitators and barriers to ASBI delivery in PHC;To estimate the parameters for the design of a definitive cRCT of ASBI in primary care in Kazahkstan, including rates of eligibility, consent, participation and retention.

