### Study processes

#### Recruitment

In both study arms, physicians will recruit patients presenting at routine care appointments. Patients potentially fulfilling the inclusion criteria will be informed about the study purpose and asked to take part. Each eligible patient who provides informed consent for study participation will be screened by a PHC physician for hazardous or harmful alcohol use using the three question Alcohol Use Disorder Identification Test – Consumption questionnaire (AUDIT-C) [48]. A show-card featuring the AUDIT-C questions and response options as well as illustrations of standard drink examples will be used as a visual aid for the screened patients. Additionally, all patients will be asked the remaining seven questions of the full AUDIT questionnaire in order to analyse correlations between AUDIT-C and full AUDIT scores [49]. The target population of the study consists of all PHC patients with risky, hazardous or harmful drinking, defined by an AUDIT-C score of four points or more for women and five points or more or for men. A full AUDIT score of 20 points or higher indicates a potential severe alcohol use disorder (AUD). If this is indicated and with the respective patient’s consent, these patients will be referred to a psychiatrist or narcologist for diagnostic assessment and treatment.

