#### Follow-up assessments

At the end of the recruitment period, participating physicians will be asked to provide their views on the implementation and potential maintenance of ASBI using structured questionnaires which will be administered by local research staff. The outcomes will inform qualitative focus groups (Table 1), which willl last approximately 60 to 90 min and will be moderated by an experienced researcher from the national study team. A semi-structured topic guide will be developed to focus discussions, drawing on key themes emerging from the structured questionnaire findings and the three major areas of interest—quality and consistency of ASBI delivered, barriers/facilitators to implementation of ASBI in PHC and the long-term sustainability of ASBI in this setting.

**Table 1 Tab1:** Key outcome measures including domains of the RE-AIM framework [54]

Dimension	Outcome measures	Assessment tool and evaluation method
Feasibility	- *Rate of eligibility*: percentage of eligible participants recruited	Case-report form; descriptive statistics
	- *Participation and retention at 3 months follow-up*: percentage of enrolled participants retained at 3 months	
Reach	- *Proportion of patients screened at baseline* Numerator: Total number of completed screens Denominator: Total number of all patients eligible for screening	
	- *Proportion of consulting patients intervened at baseline* Numerator: Total number of screen-positive patients receiving advice Denominator: Total number of patients screened positive	
Effectiveness	- *Change in AUDIT-C* score between baseline and follow-up amongst patients with risky, hazardous or harmful drinking	
Adoption	- *Proportion of staff invited that participated* Numerator: Total number of participating physicians Denominator: Total number of primary care physicians invited	
	- *Description and representativeness of staff who delivered* the screening and advice (PHC provider level)	
Implementation	- *Quality and consistency of the delivery of ASBI* given (PHC provider level; patient level) measured by quantitative interviews, provider focus groups	Provider questionnaire; provider focus groups; descriptive statistics and qualitative data analyses (content and narrative analyses)
	- *Implementation determinants* (barriers, facilitators) of ASBI delivery (PHC provider, Patient level) collected by quantitative interviews, provider focus groups	

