### Statistical analysis

Descriptive statistics will be used to evaluate quantitative outcome measures (e.g. rates of eligibility and retention). Given an anticipated drop-out rate to follow-up of 50%, statistical analyses on ASBI effectiveness will be based on the per protocol principle (PP). Due to the pilot character of the trial, a sample size calculation will not be made. However, on the basis of previous epidemiological data [55] we assume that 4000 PHC patients will need to be screened to result in a sample size of 400 patients with an AUDIT-C score of 4 or higher for women and 5 or higher for men. We anticipate a loss-to-follow-up-rate 3 months after screening of 50%, resulting in a sample size of 200 patients (i.e. 100 per group) for data analyses. By considering a moderate intra-class coefficient (ICC between 0.05 and 0.15) between the PHC units, this sample size will be sufficient to provide statistically significant results with a medium effect size (d between 0.4 and 0.6) for the analyses of the primary and secondary effectiveness endpoints. Paired *t* tests will be used for pre-post-comparison of drinking outcomes based on AUDIT-C score between baseline and follow-up within the groups. The qualitative data on the implementation processes and potential future maintenance will be summarized for a narrative analysis.

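### The only effectiveness test specified is a paired t test within each arm; no between-arm estimate is specified, and regression to the mean is likely to make each arm look improved

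*Protocol article*

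**What the plan says.** The Aim section commits to a randomised comparison: "To conduct a two-arm pilot feasibility cluster randomised controlled trial (cRCT"). The Design section allocates three primary health care units (PHCUs) to each arm. Under Recruitment, the target population is "defined by an AUDIT-C score of four points or more for women and five points or more or for men". Table 1 gives the effectiveness measure as change in AUDIT-C "score between baseline and follow-up amongst patients with risky, hazardous or harmful drinking", and the evaluation method listed for that block is descriptive statistics.

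The Statistical analysis section names one inferential procedure for effectiveness: paired t "tests will be used for pre-post-comparison of drinking outcomes based on AUDIT-C score between baseline and follow-up within the groups". Just before that it argues that the sample is adequate. It starts from "we assume that 4000 PHC patients will need to be screened to result in a sample size of 400 patients", allows 50% loss "resulting in a sample size of 200 patients (i.e. 100 per group) for data analyses", and continues "By considering a moderate intra-class coefficient (ICC between 0.05 and 0.15) between the PHC units" to conclude that this is "sufficient to provide statistically significant results with a medium effect size (d between 0.4 and 0.6").

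No test or estimate that sets one arm against the other is described anywhere in the article.

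**The concern.** A paired t test within an arm asks whether the mean score moved between two visits. It does not ask whether the intervention moved it. Three features make that gap matter here.

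- **Selection on the outcome.** Patients enter the effectiveness analysis because the baseline value of the score was high, and the same score is repeated at 3 months. Follow-up scores will fall on average with no true change in drinking.
- **An active control.** Control patients receive score feedback and a leaflet, so a genuine change in that arm is also possible. A pre-post fall in either arm cannot be attributed to the brief intervention.
- **Clustering.** The section invokes an intra-class coefficient (ICC) between PHCUs, but the paired t test treats patients as independent.

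The randomised contrast removes any fall common to both arms; the specified test does not use it. What is at stake is a reported significant reduction after the intervention that carries little information about its effect, yet could weigh in the decision on a definitive trial. The Discussion section does promise insight into potential effectiveness.

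**Working it through.** **Inputs.** From Statistical analysis: 4000 screened, 400 positive, 50% loss, 100 analysed per group, ICC 0.05-0.15, d 0.4-0.6. From Design: 3 PHCUs per arm. Assumed, because the article does not give them: two-sided 5% level, 80% power as the benchmark, and test-retest correlation r, shown as a range.

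**1. The plan's own head-count.** 4000 × 0.10 × 0.50 / 2 = 100 per group, which reproduces. The selected fraction is 400/4000 = 10%. Patients per PHCU: 100/3 = 33.3.

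**2. Regression to the mean, normal model, zero true change.** The top 10% lies above z = 1.2816. Mean of the selected = φ(1.2816)/0.10 = 1.755 SD. Variance among the selected = 1 − 1.755 × (1.755 − 1.2816) = 0.169.

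- Expected fall = (1 − r) × 1.755
- SD of change = √[(1 − r)² × 0.169 + 1 − r²]
- dz = fall / SD of change; noncentrality = dz × √100; paired t with 99 df
- Both arms significant = (per-arm probability)²

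| r | Fall (SD) | SD of change | dz | Significant, per arm | Both arms |
|---|---|---|---|---|---|
| 0.80 | 0.351 | 0.606 | 0.580 | >99.9% | >99.9% |
| 0.90 | 0.175 | 0.438 | 0.401 | 97.8% | 95.6% |
| 0.95 | 0.088 | 0.313 | 0.280 | 79% | 63% |
| 0.98 | 0.035 | 0.199 | 0.176 | 42% | 17% |

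**3. The same with a skewed 0-12 score (simulation).** Negative binomial marginal (size 0.9, probability 0.35) capped at 12, half the patients assumed to be women, and the protocol's cut-offs applied, which selects about 12.7%. Here r is the correlation on the underlying normal scale.

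| r | Mean change (points) | Significant, per arm | Both arms |
|---|---|---|---|
| 0.80 | −1.15 | 99.7% | 99.3% |
| 0.90 | −0.62 | 89% | 80% |
| 0.95 | −0.33 | 62% | 39% |

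**4. Clustering ignored by the paired test.** Design effect DE = 1 + (33.3 − 1) × ICC, which is 2.62 at ICC 0.05 and 5.85 at 0.15. If that ICC applies to change scores, the true level of a nominal 5% test is 2 × [1 − Φ(1.96/√DE)]. With 1.96/√2.62 = 1.21 this is about 23%; with 1.96/√5.85 = 0.81 it is about 42%. This is a separate source of error from regression to the mean.

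**5. What a between-arm comparison could deliver at this size.** Effective n per arm = 100/DE = 38.2 (ICC 0.05) or 17.1 (ICC 0.15). The t version uses 3 + 3 − 2 = 4 df.

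| ICC | d | Power, normal approximation | Power, 4 df |
|---|---|---|---|
| 0.05 | 0.4 | 42% | 27% |
| 0.05 | 0.6 | 75% | 51% |
| 0.15 | 0.4 | 22% | 15% |
| 0.15 | 0.6 | 42% | 27% |

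The effect detectable with 80% power (normal approximation) is 2.80 × √(2/38.2) = 0.64 to 2.80 × √(2/17.1) = 0.96. With clustering ignored, d = 0.4 needs 99 per arm, and 100 per arm gives 80.7%. Figures in step 5 take no credit for baseline adjustment, whose gain cannot be computed from the article.

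**The case against.** The best defence is that this is a pilot. Its primary aim is feasibility, its key outcomes are recruitment and retention, and AUDIT-C change is one of several additional RE-AIM measures. That stands and limits the severity. It does not rescue the test: a pilot has reason to estimate without testing, but no reason to run within-arm significance tests.

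A second defence is that the article is condensed and a fuller plan may exist. That would excuse an omission. Here a method is stated, and it is the wrong one for an effectiveness question.

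Three stronger readings are tempting, and the document does not support them.

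- **A reader might infer that both arms are bound to come out significant.** That depends on a correlation the article does not give. At 0.95 both arms are significant in 63% (normal) or 39% (skewed) of null trials, and at 0.98 in 17% (normal). Likely is supportable; certain is not.
- **A reader might infer that the arms will never be compared.** The sufficiency argument (100 per group, an ICC between units, a d) suggests that a comparison is contemplated. What can be said is that none is specified. Nor does the article propose setting one arm's p-value against the other's.
- **A reader might infer that the pilot would leave no variability estimate for planning.** The paired analysis yields each arm's mean change and SD, and a crude difference follows by subtraction. What is missing is a planned, baseline-adjusted and cluster-aware estimate with an interval.

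**Conclusion.** The point holds. In a two-arm cluster randomised trial, the only effectiveness test specified is within-arm, on patients selected for a high baseline value of the same score. With no intervention effect and 100 patients per arm, a significant fall is expected in about 79% to more than 99.9% of trials per arm under a normal model, and in about 62% to 99.7% with a skewed 0-12 score. Both ranges assume a test-retest correlation of 0.95 down to 0.8; above that range the probability drops further. Ignoring clustering is a second defect of the same test, with a size that depends on the stated ICC carrying over to change scores.

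The section is also inconsistent within itself: its case for sufficiency is framed by group and by between-unit ICC, while the test it names uses neither. For a between-arm comparison at the stated ICC and d, the sample is not sufficient at the usual 80% benchmark.

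Severity: should fix. The primary feasibility outcomes are descriptive and do not depend on this test.

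**What to change.** In the Statistical analysis section:

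1. Replace the within-arm paired t tests with one between-arm estimate of 3-month AUDIT-C, adjusted for baseline AUDIT-C and accounting for clustering by PHCU with a small-sample method, for example cluster-level summaries with 4 df. Report it with a 95% confidence interval, as estimation and not as a test of efficacy. An individual-level adjusted comparison would not do: with a design effect of 2.6-5.9, its interval would be too narrow.
2. Report within-arm means, changes and SDs descriptively, without p-values, and state that they include regression to the mean.
3. Withdraw or restate the claim that the sample will be enough for statistically significant results.

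Cost: no new data, since AUDIT-C is already collected at both visits. The price is candour about precision. The interval will be wide, with power of about 15-51% with 4 df (22-75% by normal approximation) for d 0.4-0.6 at ICC 0.05-0.15.

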### Qualitative analysis and data integration

Content analysis will be used to explore and analyse the qualitative data gathered in the structured questionnaires and provider focus groups. Qualitative content analysis represents a systematic coding and categorisation approach that can be used to identify trends and patterns within large quantities of textual data [56] and has frequently been employed in applied health research. In this study, qualitative data from the provider questionnaires and focus groups will be subject to three broad phases of analysis [57]. First, in the preparation phase, the open questionnaire response data and focus group transcriptions will be read and re-read in order to obtain a sense of the entire dataset. Second, the data will be organised, with initial open coding and categorisation of the data subsequently grouped into more refined categories and subcategories. In the final phase, the analysing process and results will be reported, through the presentation of emergent categories, and an overarching narrative. Two separate researchers will conduct the coding and categorisation of all data, with any key areas of divergence/discrepancy discussed and resolved with a third researcher. Data integration will occur primarily at the development stage, whereby themes identified in the structured questionnaire data will be used to inform the discussion topics of the provider focus groups [58].

## Discussion

Despite the fact that there are several promising implementation strategies available to policymakers and practitioners at present, uptake of ASBI remains limited and inconsistent in most countries worldwide. Moreover, we still lack a sound understanding what works, in which context, when and specifically for whom when it comes to tackling drinking in general populations.

This is the first trial to assess the feasibility of conducting a fully randomised controlled trial of the effectiveness of ASBI in primary care in Kazakhstan. By employing the pragmatic yet robust RE-AIM framework to evaluate implementation, the trial aims to deliver a comprehensive assessment of the impact of the intervention packages on the target population. Further, by exploring the feasibility and acceptability of implementing ASBI from both patients’ and physicians’ perspectives, the study also aims to provide an in-depth understanding of the processes shaping translation of ASBI into this specific setting. In doing so, the study will provide valuable new insights into the potential effectiveness of ASBI in routine PHCU practice, and an improved understanding of which factors and processes influence the effective (and thus sustainable) implementation of such interventions across Kazakhstan.

## Data Availability

No datasets were used or analysed in drafting this protocol.

## Abbreviations

ASBI: Alcohol screening and brief intervention
AUDIT: Alcohol Use Disorders Identification Test
AUDIT-C: Alcohol Use Disorders Identification Test-Consumption
CRF: Case-report form
GCP: Good Clinical Practice
ICC: Intra-class coefficient
ICH: International Conference on Harmonisation
IEC: Independent Ethics Committee
PHC: Primary health care
PHCU: Primary health care unit
RE-AIM: Reach-Effectiveness-Adoption-Implementation-Maintenance Framework
SAAPPQ: Shortened Alcohol and Alcohol Problems Perception Questionnaire
WHO: World Health Organization
